### **7.5.3. Secondary analysis : Generalization**

In the above model [5], H was elected within the set of HSR variables related with the patient health Status. There are several variables in this group called  $H_1, \dots, H_n$ . On the other hand, S was the Simpson index considered as the most usual measurement of the MB normality. However, this index is one among the multiple measurements of the MB, for which additional research is possible (cf section 7.2.2). By considering these possible variables  $S_1, \dots, S_m$ , the search of the effect of MB on Health, consists into the multivariate effect of the vector  $(S_1, \dots, S_m)$  on the vector  $(H_1, \dots, H_n)$ . This secondary analysis will be determined at the Statistical Analysis Plan level.

### **7.5.4. Limitations**

This meta-analysis has limitations: the study effect is confounded with the treatment effect, as each study assessed the placebo (or in fact with no treatment) and autologous FMT, respectively. In that sense, it will not be possible to conclude into a treatment effect. For this reason, in this exploratory analysis, we have planned the two studies in a way that selection,

|                                                                                   |                      |                                                                                               |
|-----------------------------------------------------------------------------------|----------------------|-----------------------------------------------------------------------------------------------|
| [figure not shown] | Protocol             | Protocol N°: MPOH02
EudraCT N° : 2015-004335-12
Version 10.0
Date : 20 November 2017 |
|                                                                                   | ODYSSEE STUDY |                                                                                               |

design, and other important features should be as comparable as possible to assume an absence of study effect.

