**Supplementary Table 9. Reasons for screening failure (n=37).**

|                                                          |                                                                                        |
|----------------------------------------------------------|----------------------------------------------------------------------------------------|
| Related to IMP manufacturing
n=22 (59%) | Insufficient raw material; n=14 (38%)                                                  |
|                                                          | Logistic failure; n=4 (11%)                                                            |
|                                                          | Quality control for batch release not reached; n=4 (11%)                               |
| Related to the patient
n=15 (41%)       | FMT not performed due to patients' condition; n=5 (14%)                                |
|                                                          | Patient's refusal to collection of the inoculum procedure (consent withdraw); n=3 (8%) |
|                                                          | AML diagnosis not confirmed; n=1 (3%)                                                  |
|                                                          | MDRB or C. difficile carriage at diagnosis; n=6 (16%)                           |

IMP: Investigational Medicinal Product; FMT: Fecal Microbiota Transfer; AML: Acute Myeloid Leukemia; MDRB: Multi-Drug Resistant Bacteria

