### **7.5. Individual patient Meta-analysis for a controlled result of efficacy**

#### **7.5.1. Principle**

This trial will assess the existence of an effect of AFMT on MB recovery, from MB deterioration caused by medication. However, no control group was provided. Thus it is not possible at this stage to separate the assumed MB recovery caused by AFMT from a natural evolution that should otherwise have been measured in a control placebo group. Another observational study [ULYSSE study] has been planned conjointly with the same patient selection and measurements. The observational study will then provide us with a control group through an individual patient data (IPD) meta-analysis.

|                                                                                                         |                      |                                                                                               |
|---------------------------------------------------------------------------------------------------------|----------------------|-----------------------------------------------------------------------------------------------|
| [figure not shown]
MaaT Pharma | Protocol             | Protocol N°: MPOH02
EudraCT N° : 2015-004335-12
Version 10.0
Date : 20 November 2017 |
|                                                                                                         | ODYSSEE STUDY |                                                                                               |

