### **7.5.2. Inferential Aspects**

We plan to conduct an Individual Patient Meta-analysis (IPDM) aiming at assessing the AFMT effect compared with no treatment in recovering the initial MB previously deteriorated by medication.

The inferential model will be:

$$HR_i = k_0 + k_b.H_i + k_c.S_i + k_t.FMT + \eta.center \quad \text{where for } i=b,d,t \quad [4]$$

This model is similar to [1] except that a treatment effect (FMT) is coded 1 or 0, following that the patient has been administered AFMT (in this study) or not (in the observational study). As the decision to treat or not has not been randomized and originates from two separate studies, the comparison between baseline values of the two studies will identify variables  $X_i$  for which differences were identified on the two studies, and the used model will be adjusted for these variables as shown in the following model [5]

$$HR_i = k_0 + k_b.H_i + k_c.S_i + k_t.FMT + \eta.center + \sum w_i X_i \quad \text{where for } i=b,d,t \quad [5]$$

The above mentioned models [2] and [3] assessing the direction of the effect HS-S will be conducted by adding the main treatment (FMT) effect.

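### Models [4] and [5] code AFMT by study at every visit, including two before AFMT, so the coefficient mixes study or selection differences with treatment and the pre-AFMT data go unused as a check

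*Protocol*

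**What the plan says.** Section 7.5.1 grants that a single-arm trial cannot separate recovery due to AFMT from natural recovery, and names the control: "Another observational study [ULYSSE study] has been planned conjointly with the same patient selection and measurements". Section 7.5.2 aims to assess AFMT against no treatment and writes the models out. In model [4], "a treatment effect (FMT) is coded 1 or 0, following that the patient has been administered AFMT (in this study) or not". The model runs over i = b, d, t, and FMT has no time index. (I read t as the final, D40, time.) For comparability, "the comparison between baseline values of the two studies will identify variables" that differ, and these enter model [5] as covariates. Section 7.5.4 states that "the study effect is confounded with the treatment effect", that a treatment effect cannot therefore be concluded, and that the analysis is exploratory. It adds that the studies were planned so that selection, "design, and other important features should be as comparable as possible to assume an absence of study effect".

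On timing, section 6.4.2 collects the Visit 2 sample around D29, within three days before antibiotics stop, and gives AFMT 24 hours after they stop (D30 and D31). Section 7.1.1 labels this sample D30, but it still precedes AFMT.

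**The concern.** At times b and d no ODYSSEE patient has received AFMT, so whatever the FMT term picks up there cannot be treatment. It is a difference between the studies or between the kinds of patient who remain in them. Because one coefficient, k_t, spans all three times, it pools that difference with any AFMT effect at D40.

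The protocol assumes this difference away, although it could be estimated from data that, on the protocol's description, both studies measure. A baseline comparison cannot see a difference that arises during induction. That is a plausible place for one: ODYSSEE patients coded 1 must reach D30 without persistent mucositis, colitis or haemorrhoids and with a usable inoculum (sections 5.2 and 6.4.2). ULYSSE may not apply the same filters, since an observational study needs no inoculum; its protocol is not at hand. At stake is the only comparison in the plan against patients not given AFMT.

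**Working it through.** **Inputs.** ODYSSEE n = 20 (section 6.3). Within-patient correlation 0.5 (section 7.1.2's companion section 7.1.1 assumes at least this for the deterioration and final values; here it is applied to every pair of visits). The ULYSSE sample size is not given: 20 is assumed unless stated, with ranges shown. SD is the between-patient SD at one visit, set to 1. Section 7.5 states no sample size, power or alpha, so there is no figure of the plan's own to reproduce.

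**1. What k_t estimates.** Leave out the H, S and centre terms, let D_b, D_d and D_t be the between-study differences at the three times, and let τ be an AFMT effect present only at t. With FMT coded by study at every time,

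k_t = (D_b + D_d + D_t + τ)/3.

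- Constant study difference δ, τ = 0: k_t = δ.
- Difference arising between D0 and D29 and persisting, τ = 0: k_t = 2δ/3.
- No study difference, τ = 0.6: k_t = 0.6/3 = 0.20.

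A constant study difference therefore enters whole, and a genuine D40 effect is cut to a third.

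**2. Simulation of this simplified model** (4,000 runs, 20 v 20, two-sided 5%, no AFMT effect, constant study difference):

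| Study difference (SD) | Mean k_t as coded | Significant | Significant, D29-to-D40 difference in change |
|---|---|---|---|
| 0.3 | 0.31 | 21% | 5% |
| 0.5 | 0.50 | 47% | 5% |
| 0.8 | 0.80 | 85% | 6% |

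With no study difference and τ = 0.6, mean k_t as coded is 0.20 and significant in 12% of runs. The difference in change averages 0.60 and is significant in 46%.

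**3. What the baseline check sees.** Let the difference arise between D0 and D29 (20 v 20):

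| Difference (SD) | Flagged by D0 comparison | Flagged by D0-to-D29 contrast | Mean k_t as coded |
|---|---|---|---|
| 0.3 | 6% | 15% | 0.20 |
| 0.5 | 5% | 33% | 0.33 |
| 0.8 | 5% | 70% | 0.53 |

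The D0 comparison stays at its 5% error rate. The D0-to-D29 contrast does better, but is weak for small differences.

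**4. Precision of the D0-to-D29 contrast.** Half-width = t(0.975) × √(1/20 + 1/n₂), in SDs of the change. At correlation 0.5 the SD of a change is √(2 × (1 − 0.5)) = 1, so the units agree with those above.

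- n₂ = 20: 0.64
- n₂ = 40: 0.55
- n₂ = 60: 0.51

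**The case against.** The strongest reply is that the protocol already deals with this. It admits the confounding, bars a treatment-effect conclusion, calls the analysis exploratory, and compares and adjusts baseline values. Much of that stands. A reader might infer that comparability is wholly unchecked, or that the plan will report a study difference as an AFMT effect. The text supports neither: baseline is checked, and section 7.5.4 forbids the conclusion. What remains is that k_t is built to absorb the difference and that no estimate of the difference is planned beside it.

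A second reply is that a sensitivity contrast belongs in the SAP. But section 7.5.2 writes the models, the coding and the adjustment rule in full. Within 7.5 only the multivariate generalisation (7.5.3) is left to the SAP.

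A third is that the pre-AFMT coefficient is not a pure study effect, because selection of patients who reach and qualify for AFMT can enter it. That is correct, and it is described here as a study or selection difference.

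A fourth is that the D0-to-D29 contrast does not observe recovery after D30. This also stands. A study difference of 0.3 to 0.5 SD confined to the D29-to-D40 change would make a two-group test of that change significant in 15% to 34% of analyses with 20 controls, and 21% to 48% with 60. The plan contains no such test, so these are not its error rates. They show what even the repaired term would remain exposed to.

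Finally, a reader might infer from Supplementary Table 9 (22 of 37 screen failures related to manufacturing) that untransplanted ODYSSEE patients could serve as untreated controls. The table is a later result, nothing shows that these patients gave D29 or D40 samples, and they are themselves selected.

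**Conclusion.** The point holds in a limited form. As written, k_t in models [4] and [5] combines any study or selection difference with the AFMT effect, because FMT equals study membership at two visits that precede AFMT. The D0-to-D29 response and the D29 state are not compared between studies, so the assumption in section 7.5.4 is checked at baseline only.

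In the simplified model a constant study difference passes one-for-one into k_t (21% to 85% false significance for 0.3 to 0.8 SD), and an AFMT effect seen only at D40 is diluted to a third. These figures rest on an assumed 20 controls, correlation 0.5 throughout, and omission of the H, S and centre terms. That ULYSSE has D29 data is inferred from the statement that it shares ODYSSEE's selection and measurements.

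The paired co-primary analysis (section 7.3.1) is unaffected. This is an inexpensive improvement to an exploratory comparison. It would not make an AFMT effect identifiable, and a small pre-AFMT contrast would not license attributing the later term to AFMT.

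**What to change.** - **Section 7.5.2:** add a study term and set FMT to 1 only for ODYSSEE patients at the post-AFMT time, so that k_t is the between-study difference in the D29-to-D40 change. For k_t to have exactly that meaning, enter visit as a factor, let the study difference be free at D0 and at D29, and omit the lagged health term. With one constant study term and equal correlations, k_t would compare D40 with the D0/D29 average, and a persisting difference δ that arose during induction would still leak in as δ − (0 + δ)/2 = δ/2.
- **Beside k_t:** report the between-study D0-to-D29 contrast in the Simpson index and in the HSR variables, as an estimate with 95% CI and not as a pass/fail test.
- **Section 7.5.4:** keep the statement that a treatment effect cannot be concluded. Replace the assumed absence of a study effect by this reported estimate, and say that it cannot detect differences arising only after D30.

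The cost is wording, one study term and one contrast. No new samples are needed if ULYSSE measured D29 as described. The drawback is imprecision: about 0.64 to 0.51 SD either side with 20 to 60 controls, so a contrast near zero does not establish comparability.

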## 7.6. Procedures

The interim analyses will be conducted in a way to avoid any perceived bias about the results.

A SAP will be provided before starting the analysis.

Data entry will be organized as to provide a real time estimate of the existing sample.

## 8. DATA MANAGEMENT

- CRF management: CRF redaction and CRF filling and completion will be supported by local Clinical Research Associate (CRA) for each centre of investigation
- Data entry will be done in each centre in a common frame
- Data fusion to create a single unique database will be performed with the help of the statistician, or by a CRO before starting statistical analysis
- A final data procedure for starting statistical analysis will be written in the statistical plan included in the protocol.

## 9. SAFETY EVALUATION

### 9.1. Adverse event reporting system

#### 9.1.1. Definitions

According to the code of Public Health (R1123-39):

- Adverse event (AE)

An AE is defined as any untoward medical occurrence in a patient or clinical investigation subject administered a pharmaceutical product and that does not necessarily have a causal relationship with this treatment. An AE can therefore be any unfavourable and unintended sign, symptom or disease temporally associated with the use of a investigational medicinal product, whether or not related to the investigational medicinal product.

- Serious adverse event (SAE)

---

All documentation of **MaaT Pharma** is PROPRIETARY information and may not be forwarded to third parties without prior written consent from **MaaT Pharma**. Reproductions, either in part or in whole, may not be published or copied in any manner, without the explicit written consent of **MaaT Pharma**

|                                                                                   |                      |                                                                                               |
|-----------------------------------------------------------------------------------|----------------------|-----------------------------------------------------------------------------------------------|
| [figure not shown] | Protocol             | Protocol N°: MPOH02
EudraCT N° : 2015-004335-12
Version 10.0
Date : 20 November 2017 |
|                                                                                   | ODYSSEE STUDY |                                                                                               |

A SAE is defined as any untoward medical occurrence that at any dose:

- results in death,
- is life-threatening,

Note: The term “life-threatening” in the definition of “serious” refers to an event in which the subject was at risk of death at the time of the event; it does not refer to an event which hypothetically might have caused death if it were more severe.

- requires in patient hospitalization or prolongation of existing hospitalization,
- results in persistent or significant disability/incapacity,
- is a congenital anomaly and/or birth defect,
- jeopardizes the participant and may require medical or surgical treatment to prevent one of the preceding outcomes.

Medical and scientific judgment should be exercised in deciding whether expedited reporting is appropriate in other situations, such as important medical events that may not be immediately life-threatening or result in death or hospitalization but may jeopardize the subject or may require intervention to prevent one of the other outcomes listed in the definition above.

- New development

Any new safety data:

- which could significantly alter the benefice/risk balance evaluation of the advanced therapy product or the study
- or which could lead to consider modifications regarding the advanced therapy or the conduct of the study

For examples:

- A SAE that could be linked to the investigation and diagnostic procedures of the study and that could change the course of this study
- A significant risk for the study population (e.g. lack of efficiency of the investigational medicinal product used in the treatment of a life-threatening disease)
- Significant results from animal studies recently completed

|                                                                                                         |                      |                                                                                               |
|---------------------------------------------------------------------------------------------------------|----------------------|-----------------------------------------------------------------------------------------------|
| [figure not shown]
MaaT Pharma | Protocol             | Protocol N°: MPOH02
EudraCT N° : 2015-004335-12
Version 10.0
Date : 20 November 2017 |
|                                                                                                         | ODYSSEE STUDY |                                                                                               |

- Early discontinuation or temporary interruption for safety reasons of a clinical trial conducted in another country with the same investigational medicinal product
- An unexpected SAE to a non-investigational medicinal product required to conduct the study (e.g. challenge agents, emergency treatment)

The AE intensity is evaluated by the investigator according to the following classification:

- **Mild:** Awareness of signs or symptoms, but easily tolerated and are of minor irritant type causing no loss of time from normal activities. Symptoms do not require therapy or a medical evaluation; signs and symptoms are transient.
- **Moderate:** Events introduce a low level of inconvenience or concern to the participant and may interfere with daily activities, but are usually improved by simple therapeutic measures; moderate experiences may cause some interference with functioning
- **Severe:** Events interrupt the participant's normal daily activities and generally require systemic drug therapy or other treatment; they are usually incapacitating

### **9.1.2. Investigator responsibilities**

#### **9.1.2.1. Regulatory obligations of the investigator (Art. R. 1123-54)**

All SAE should be reported immediately to the sponsor except for those SAE that the protocol (cf section 9.1.2.2.1) identifies as not needing immediate reporting.

Thus, investigators must report all events with one of the following criteria:

- Death
- Impairment of vital prognosis
- Require or extend hospitalization
- Long-lasting damages
- Congenital abnormalities/ birth defect
- Any AE judged as clinically significant

|                                                                                                         |                      |                                                                                               |
|---------------------------------------------------------------------------------------------------------|----------------------|-----------------------------------------------------------------------------------------------|
| [figure not shown]
MaaT Pharma | Protocol             | Protocol N°: MPOH02
EudraCT N° : 2015-004335-12
Version 10.0
Date : 20 November 2017 |
|                                                                                                         | ODYSSEE STUDY |                                                                                               |

#### **9.1.2.2. Protocol specificities**

##### **9.1.2.2.1. Events that do not require an immediate report by the investigator**

In the frame of this protocol, the following events will not require an immediate notification to the Sponsor and therefore will not be subject to expedited reporting to the Competent Authorities and Ethics Committees:

- Fever > 38°C occurring within 7 days of AFMT
- Abdominal pain within 7 days of AFMT
- Bloating within 7 days of AFMT
- Diarrhea within 7 days of AFMT

Moreover, a predefined list of events specifically known to be related to chemotherapy was set up. These events will not require an immediate notification to the Sponsor and therefore will not be subject to expedited reporting process.

- Neutropenia
- Thrombocytopenia
- Electrolytes deficiency
- Hypoalbuminemia
- Tumor lysis syndrome
- Hepatic cholestasis / cytotoxicity

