### ***D30 and D31 (between D25 and D36 depending on patient's condition) - Fecal transplantation***

The AFMT will be performed 24 hours after antibiotics discontinuation and after aplasia completion. The patient will receive 2 inocula of 150 mL corresponding to a total of 60g (2 x 30g) of faeces, according to the procedure (**Appendix 1**). A rectal preparation for AFMT will include 2 enemas with "Normacol lavement" the night before and the morning of the procedure, enhancing the potential for FMT to provide a "fresh start" in repopulating the colonic habitat of the patient. Indeed, the lavage will enhance FMT success by flushing out residual faeces, antibiotics, and *C. difficile* bacteria, toxins and spores (83). The rectal preparation and AFMT will not be performed in case of persistent mucositis, colitis, or haemorrhoids, that constitute exclusion criteria. A third inoculum is available in case of technical incident (rejection of the inoculum by the patient within 1 hour after transplantation). Fecal transplantation is performed by a rectal probe introduced in the patient's rectum. A tubing, ending with a rectal probe, is directly connected to allow the inoculum to reach the colon. The patient will remain in lying position for 1 hour to ensure a good transplantation and avoid any loss. Patient's vital signs (blood pressure, pulse, temperature, respiratory rate) will be monitored during all the time of the transplantation process, until the expulsion of the remaining transplant but at least 2 hours after AFMT. Monitoring will also focus on the recovery of intestinal transit, onset of abdominal pain, occurrence of fever before the patient's hospital discharge. In case of severe adverse event, the hospitalization will be extended to treat the event. In case of procedure-related SAE or SADR (Serious Adverse Drug Reaction) during the first AFMT, the second AFMT will not be done. Post-transplant clinical tolerance will be monitored with a questionnaire (**Appendix 1**) and the logbook (**Appendix 2**).

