### ***D40 (between D35 and D 45 depending on patient's condition)- Visit 3 - Hospitalization for consolidation chemotherapy***

At this time, the patient will report to the physician any adverse reaction or severe event occurred since his hospital withdrawal using the logbook during admission visit. Particular attention will be given for occurrence of severe diarrhea, fever, abdominal pain, infectious events and concomittant medications. The patient will also receive a EQ-5D-5L questionnaire. Prior to the initiation of consolidation chemotherapy, faeces and blood will be collected for analysis (**Procedures will be provided by BIOFORTIS SAS** - biochemical and bacteriological

|                                                                                                         |                      |                                                                                               |
|---------------------------------------------------------------------------------------------------------|----------------------|-----------------------------------------------------------------------------------------------|
| [figure not shown]
MaaT Pharma | Protocol             | Protocol N°: MPOH02
EudraCT N° : 2015-004335-12
Version 10.0
Date : 20 November 2017 |
|                                                                                                         | ODYSSEE STUDY |                                                                                               |

analysis, control of the microbiota recovery by metagenomic and analysis of blood immune cells).

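### The chemotherapy-type exemption from immediate reporting has no time limit and no causality condition, so for some serious events between AFMT and consolidation the reporting sections conflict

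*Protocol*

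**What the plan says.** Protocol section 9.1.2.1 requires immediate reporting of every serious adverse event "except for those SAE that the protocol (cf section 9.1.2.2.1) identifies as not needing immediate reporting". Section 9.1.2.2.1 then gives two lists.

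- The first covers fever, abdominal pain, bloating and diarrhea. Each item carries its own limit, as in "Fever > 38°C occurring within 7 days of AFMT".
- The second is introduced with the words "a predefined list of events specifically known to be related to chemotherapy was set up". It covers neutropenia, thrombocytopenia, electrolyte deficiency, hypoalbuminemia, tumor lysis syndrome, and hepatic cholestasis or cytotoxicity. Its rule is: "These events will not require an immediate notification to the Sponsor and therefore will not be subject to expedited reporting process".

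On timing, section 6.4.2 heads the transplantation step "D30 and D31 (between D25 and D36" and sets its condition: "The AFMT will be performed 24 hours after antibiotics discontinuation and after aplasia completion". Visit 3 is headed "D40 (between D35 and D 45" and places sampling ahead of the next cycle: "Prior to the initiation of consolidation chemotherapy, faeces and blood will be collected for analysis".

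**The concern.** The second list is justified by a known link to chemotherapy. That phrase explains why the list exists; it is not a test applied to each event. The list is tied neither to a chemotherapy date nor to the investigator's causality opinion. Events are recorded from consent to the last planned visit (9.1.2.3.1), so the exemption runs throughout the study.

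AFMT falls after the induction aplasia and before consolidation. In those days attribution to chemotherapy by category alone is at its weakest, and a new serious hepatic, electrolyte or cytopenic event deserves an individual causality judgement. During the first week both lists apply together, so diarrhea and a serious electrolyte deficiency accompanying it would both be exempt.

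The stake is speed. The sponsor's 7-day and 15-day clocks in 9.1.3.1 run from receipt of the report, and the protocol's sample-size text describes this as a first-in-man trial.

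**Working it through.** No power, rate or error probability is involved. The check has two parts: the length of the interval, and a comparison of the reporting sections.

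**Interval between AFMT and consolidation** (visit days from 6.4.2)

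- Nominal, from the second AFMT: D40 − D31 = 9 days.
- Nominal, from the first AFMT: D40 − D30 = 10 days.
- Longest within the windows: D45 − D25 = 20 days.
- Shortest: the AFMT window ends at D36 and the Visit 3 window opens at D35, so the interval can shrink to almost nothing.

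The protocol does not name this interval; it follows from the schedule.

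**Reporting sections side by side**

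| Section | Rule for a serious event on the second list |
|---|---|
| 9.1.2.1 | Immediate report, with life-threatening events and hospitalization among the criteria, but with an exception for whatever 9.1.2.2.1 exempts |
| 9.1.2.2.1 | Exempt, with no time window and no causality condition |
| 9.1.2.2.2 | Immediate report of septic shock, intestinal perforation, death and extension of hospitalization |
| 9.1.2.3.2 | Immediate procedure for a serious event, form within 1 day; the exemption is not repeated |

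**Working through the cases after AFMT**

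1. A listed event that is fatal or prolongs the stay is caught by 9.1.2.2.2.
2. A severe listed event before discharge leads to an extended stay under the transplantation text of 6.4.2, so 9.1.2.2.2 catches it as well.
3. A life-threatening listed event without death or a prolonged stay is exempt under 9.1.2.2.1 and absent from 9.1.2.2.2, yet immediately reportable under 9.1.2.3.2. The sections conflict.
4. A listed event that causes a new admission after discharge meets the same conflict. The case can arise, because the Visit 3 text asks for events since the patient left hospital.
5. For a listed event thought possibly related to AFMT, 9.1.2.3.1 records that opinion in the case report form, but 9.1.2.2.1 makes no use of it. The same section removes the event from expedited reporting, while 9.1.3.1 has the sponsor report any suspected unexpected serious event.

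Cases 3 to 5 are the gap.

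**Frequency.** Supplementary Table 6 totals 30 severe events after the first 24 hours in 25 treated patients: 1 in the blood class, 1 in the metabolism class, no hepatobiliary row, so 1 + 1 = 2 of 30 in the classes closest to the list. The table counts severe rather than serious events, gives organ classes rather than terms, and is not restricted to this interval. It cannot be turned into a rate for the gap.

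**The case against.** The strongest reply is that the protocol already contains the safeguards. Section 9.1.2.2.2 covers death and extended hospitalization, 6.4.2 extends the stay for a severe event around AFMT, and 9.1.2.3.2 asks for immediate reporting without repeating the exemption. Every event is recorded with its onset date and the investigator's causality opinion. This stands, and it narrows the point considerably. It does not close cases 3 to 5, because 9.1.2.1 and 9.1.2.2.1 expressly create an exemption that 9.1.2.3.2 ignores.

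It is also fair that days without chemotherapy dosing are not days without chemotherapy effects. Late effects of induction remain possible, and the documents do not show that AFMT causes any listed event. The argument is for an individual causality judgement, not for a presumption of harm.

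Four stronger readings are tempting and are not supported.

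- A reader might infer that every serious listed event after AFMT escapes immediate reporting. Sections 9.1.2.2.2 and 6.4.2 show otherwise.
- A reader might attach an expected count. An assumed risk of 5% to 15% would give 0.05 × 20 = 1 to 0.15 × 20 = 3 events in 20 patients, but nothing in the documents supports that range.
- A reader might call this the only interval in which AFMT safety can be read without chemotherapy running. The protocol does not say so; follow-up lasts to month 12, and it does not state that chemotherapy continues throughout.
- A reader might conclude that the data safety monitoring board would be advised late or the second AFMT wrongly given. The board's data flow rests on a charter that is not shown, and withholding the second AFMT depends on an event during the first, not on notice to the sponsor.

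**Conclusion.** The point holds in a limited form. The second list is unbounded in time and independent of causality, and it reaches serious events, so it covers the days between AFMT and consolidation, where its stated ground is weakest. The exposed interval is nominally 9 to 10 days per patient and at most 20 within the windows. Within it, the gap is confined to listed events that are serious for reasons other than death or extended hospitalization, and for these 9.1.2.1, 9.1.2.2.1, 9.1.2.2.2 and 9.1.2.3.2 give conflicting instructions. The cost of the gap is delayed notification; no data are lost. How often it would matter cannot be estimated from the documents.

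The conclusion rests on two readings: that the exception in 9.1.2.1 means what it says, and that consolidation does not begin before the Visit 3 sample, as 6.4.2 states.

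**What to change.** Add a sentence to 9.1.2.2.1 stating that the chemotherapy-list exemption does not apply in two situations:

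- a serious listed event with onset or worsening from the first AFMT until the start of the next chemotherapy or the end of the Visit 3 window (D45), whichever comes first;
- any serious listed event, at whatever time, that the investigator considers possibly related to AFMT.

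Both then follow the immediate-reporting rule of 9.1.2.1. The D45 limit closes the window for a patient who receives no further cycle and caps it at D45 − D25 = 20 days for AFMT given within schedule. Align 9.1.2.1, 9.1.2.2.2 and 9.1.2.3.2 with this text, so that each states the same exemption and the same exceptions to it.

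The cost is a wording change in the safety section and a few additional immediate reports. Treatment, visits and data collection are unchanged.
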